### Participant timeline {13}

Figure 2 depicts participants’ recruitment and randomization, the study procedures and the outcomes of the study. Patients admitted for COVID-19 to the ICU of the participating hospitals will be invited to a post-COVID-19 outpatient clinic 3 months after hospital discharge as part of the regional standard of care. All patients will receive an information letter and will be contacted by telephone to discuss participation 1 month prior to this visit. During the outpatient clinic visit, informed consent will be obtained and patients will be randomized. Patients randomized to the early ICU-VR group will receive ICU-VR during the same visit, whereas patients randomized to the late ICU-VR group will receive ICU-VR during a second outpatient clinic visit 3 months later (i.e. 6 months after hospital discharge). Questionnaires will be sent at 3 months (prior to the first outpatient clinic visit), 4 months, 6 months (prior to the second outpatient clinic visit for patients in the late intervention group), 7 months and 12 months after hospital discharge.

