**Fig. 2 Fig2:**
[figure not shown]
Flow diagram of the study. Abbreviations: COVID-19, coronavirus disease 2019; EQ-5D, European Quality of life 5 dimension questionnaire; HADS, Hospital Anxiety and Depression Scale; ICU, intensive care unit; ICU-VR, intensive care unit-specific virtual reality; IES-R, Impact of Event Scale–Revised. Eligible patients will be invited to a post-COVID outpatient clinic and randomized across the early and late ICU-VR group. The early group will receive the ICU-VR intervention during the same visit, while the late group receives ICU-VR during a second outpatient clinic visitation 6 months after hospital discharge. Psychological well-being and quality of life will be assessed 3, 4, 6, 7 and 12 months after hospital discharge using follow-up questionnaires

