### Sample size {14}

In the previously conducted pilot study examining the feasibility, safety and clinical relevance of ICU-VR in sepsis survivors, we identified an effect size Cohen’s *d* of 0.77 [33]. Due to the non-normality of PTSD scores after 6 months, these calculations could represent an overestimation of the sample size. We consider the effect estimates for the ICU-VR module to be similar to the intervention group, as was tested in our pilot study. A G*Power analysis revealed that 80 patients have to be included in the study to detect such an effect size, using a two-sided alpha of 0.05, a power of 0.80, a 1:1 randomization and an expected loss to follow-up of 20% based on our pilot study. We will include patients from June 2020 to December 2020. When the minimum required number of patients is reached prior to December 2020, inclusion will be continued until December 2020. When the minimum required number of patients is not reached in December 2020, inclusion will be continued until the minimum required sample of 80 patients is reached.

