## Statistical methods

### Statistical methods for primary and secondary outcomes {20a}

Baseline demographics and treatment-related characteristics will be quantified using descriptive statistics. Continuous variables will be presented as medians (95% range). Categorical variables will be presented as absolute numbers and relative frequencies.

Differences between study groups in continuous variables, such as the IES-R sum score, the HADS anxiety and depression scores, the RAND-36 subscales and the EQ-5D utility score, at several follow-up time points will be analysed using a mixed effect linear regression model with a random intercept for each study site. Patients will also be categorized based on clinically meaningful cut-offs for the IES-R sum score and the HADS anxiety and depression scores. An IES-R sum score ≥ 24 will be considered as clinically relevant PTSD; a HADS anxiety or depression score > 8 will be considered as clinically relevant anxiety or clinically relevant depression, respectively [36, 41, 46]. Differences in categorical variables between study groups at several follow-up time points will be analysed using a mixed effect logistic regression model with a random effect for each site. Differences in continuous or categorical variables throughout follow-up will be analysed using a mixed effect linear or logistic regression model with an interaction variable of time*randomization and a random intercept and/or slope for each individual and each study site as appropriate.

To determine whether there are time-specific windows of opportunity (3 or 6 months after hospital discharge) for the effect of ICU-VR, we will analyse psychological impairments and quality of life 1 month (4 and 7 months after hospital discharge in the early and late intervention groups, respectively), 3 months (6 and 9 months after hospital discharge in the early and late intervention groups, respectively) and 6 months after receiving ICU-VR (nine and 12 months after hospital discharge in the early and late intervention groups, respectively) using mixed effect linear/logistic regression models with a random intercept for each site and an interaction variable time*randomization.

All data will be gathered using Castor EDC. All analyses will be performed using SPSS (version 24.0; SPSS Inc., Chicago, IL) and R for Statistics (R Foundation for Statistical Computing, Vienna, Austria, 2015). A *P* value ≤ 0.05 will be considered statistically significant.

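### The window-of-opportunity analysis aligns the groups on time since ICU-VR, so its group contrast mixes the timing of ICU-VR with three further months of natural course, in an unknown direction

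*Protocol article*

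**What the plan says.** The third paragraph of the Protocol article's Statistical methods {20a} opens with its purpose: "To determine whether there are time-specific windows of opportunity (3 or 6 months after hospital discharge) for the effect of ICU-VR". It names three comparisons, each at a fixed time since ICU-VR:

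- The first is at "1 month (4 and 7 months after hospital discharge in the early and late intervention groups, respectively".
- The second, 3 months after exposure, sets the early group at month 6 against the late group at month 9.
- The third, half a year after exposure, is at "nine and 12 months after hospital discharge in the early and late intervention groups, respectively".

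The analysis is to be done "using mixed effect linear/logistic regression models with a random intercept for each site and an interaction variable time*randomization". No term for months since discharge, no pre-exposure score and no patient effect is stated for this analysis.

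The assessment schedule is in the legend of Fig. 2: "Psychological well-being and quality of life will be assessed 3, 4, 6, 7 and 12 months after hospital discharge". Participant timeline {13} places a questionnaire before each exposure: "Questionnaires will be sent at 3 months (prior to the first outpatient clinic visit), 4 months, 6 months (prior to the second outpatient clinic visit", the second of these visits being for the late group. Randomisation takes place at the 3-month visit (Implementation {16c}).

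**The concern.** Randomisation at 3 months makes the groups comparable at the same number of months after discharge. It does not make the early group at 4 months comparable with the late group at 7 months. Each of the three comparisons gives the late group 3 extra months of whatever happens to ICU survivors over time. With two groups and a constant offset, the group term is the timing effect plus 3 months of natural course, and the data in that comparison cannot split the two.

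The Discussion calls the best timing of ICU-VR unknown and gives the possible benefit of a later intervention as the reason for studying exposure at 6 months. A result at P ≤ 0.05 could therefore be read as evidence on when to offer ICU-VR in aftercare, even if timing made no difference. A larger sample would not cure this; it would make a false difference more likely to reach significance.

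**Working it through.** **Inputs.** From Sample size {14}: 80 patients, d = 0.77, two-sided alpha 0.05, power 0.80, 1:1 allocation, 20% loss. From Statistical methods {20a}: the aligned months. Assumed, because the document gives no figure: natural change of r SD per month, and within-patient correlation rho.

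**The plan's own figure.** The window analysis has no stated figure, but the sample size gives the number per arm. The Limitations section says no distribution was assumed. A Wilcoxon-Mann-Whitney test at its minimum relative efficiency (0.864) with d = 0.77 needs 32 per arm (power 0.803), and 64/0.80 = 80. The stated total is reproduced. Completers per arm: 80 × 0.80/2 = 32.

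**Which aligned points have data.** Months since ICU-VR at each later questionnaire:

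- Early (exposed at 3): 4−3, 6−3, 7−3, 12−3 = 1, 3, 4, 9
- Late (exposed at 6): 7−6, 12−6 = 1, 6

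The only shared point is 1 month. The 6 v 9 comparison lacks the late group and the 9 v 12 comparison lacks the early group, because nobody is assessed at 9 months.

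**Bias of the level contrast, no true timing effect.** False difference = (7 − 4) × r = 3r. In SD units the SE with 32 per arm is sqrt(2/32) = 0.25. P(significant) = Φ(−1.96 + 3r/0.25) + Φ(−1.96 − 3r/0.25).

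| r (SD/month) | False difference (SD) | z shift | Normal | Noncentral t |
|---|---|---|---|---|
| 0 | 0 | 0 | 5% | 5% |
| 0.05 | 0.15 | 0.6 | 9.2% | 9.1% |
| 0.10 | 0.30 | 1.2 | 22.4% | 21.9% |
| 0.15 | 0.45 | 1.8 | 43.7% | 42.6% |

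A simulation of the 4 v 7 month contrast with site adjustment (500 runs each) gave mean late-minus-early symptom differences of −0.15 and −0.31 SD at r = 0.05 and 0.10, significant in 9% and 22% of runs. At r = 0 it gave 6.4%. The value r = 0.15 was not simulated.

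**The interaction term.** If change is linear, both groups have slope r per month and the offset cancels, so time*randomization carries no bias. It is biased only if recovery is non-linear. Take an assumed decelerating curve exp(−(t−3)/6), with 1 SD still to be recovered at month 3. The false level gap is 0.333 SD at 4 v 7 months and would be 0.239 SD at 6 v 9. The gap shrinks by 0.094 SD, so the interaction leans towards early while the level leans towards late.

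**Change from the pre-exposure score** (not stated in the plan), same curve: −0.154 SD from month 3 to 4 and −0.093 SD from month 6 to 7. This false difference of 0.061 SD favours early. The confounding remains, with its sign reversed.

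**Precision of a comparison at equal time since discharge.** The window contrast is (early minus late, change 3 to 4) minus (late minus early, change 6 to 7). In each arm it has weights −1, +1, −1, +1 on months 3, 4, 6, 7. With equal variances and common correlation rho its variance is 2 × 4(1 − rho)/32 = 0.25(1 − rho), so SE = 0.5 × sqrt(1 − rho).

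| rho | SE (SD) | Ratio to 0.25 |
|---|---|---|
| 0.30 | 0.418 | 1.67 |
| 0.50 | 0.354 | 1.41 |
| 0.75 | 0.250 | 1.00 |

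**The case against.** The strongest reply is about scope. The window question is not among the objectives {7} or outcomes {12}. The primary outcome is the effect of early ICU-VR up to 6 months, and the other between-group and follow-up analyses in {20a} compare the groups at the same time since discharge. That stands: a reader might infer that the main result of the trial is compromised, and the document does not support this.

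Second, a reader might infer that the analysis must favour late ICU-VR. That needs both improvement over time and a comparison of levels. The document gives no recovery rate, worsening would reverse the sign, and a change-score analysis could reverse it too. Only confounding in an unknown direction is supported.

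Third, the protocol does not say which coefficient or rule would declare a window. The percentages hold only if the group level difference at 4 v 7 months is the test. Under the same linear assumption the interaction is unbiased, so they are not error rates of the analysis as a whole. This stands as well.

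Fourth, comparing at equal time since discharge is not a full cure. After month 6 no unexposed group remains, so the effect of late ICU-VR rests on an assumption, and the interval is usually wider. This is correct and belongs in the fix. None of these points removes the confounding in the group contrast, and nothing elsewhere in the document adjusts for it.

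**Conclusion.** The concern holds for a supplementary analysis and should be fixed. The group contrast aligned on time since ICU-VR cannot separate the timing of exposure from 3 months of natural course. That follows from the design and needs no assumption. Its size does need one: 0.15 to 0.45 SD for an assumed change of 0.05 to 0.15 SD per month, with about 9% to 44% false-positive results if the level difference is tested with 32 per arm. With no natural change there is no bias.

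The same sentence also conflicts with the schedule. Two of its three comparisons need a 9-month assessment that the Participant timeline {13}, the legend of Fig. 2 and section {18a} do not contain.

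**What to change.** - Estimate the 1-month effects at equal time since discharge, from one model with categorical month since discharge, a patient effect and the site term. ICU-VR at 3 months: early minus late in change from month 3 to 4. ICU-VR at 6 months: late minus early in change from month 6 to 7. Compare the two and label the result exploratory.
- State the assumption that the early group's effect is stable from month 6 to 7, and that the contrast answers only the 1-month question.
- If a comparison aligned on time since ICU-VR is kept, report it as descriptive, non-randomised and confounded with time since discharge.
- Remove the 6 v 9 and 9 v 12 month contrasts, or reconcile them with the assessment schedule.

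The cost is analysis wording; months 3, 4, 6 and 7 are already collected. The price in precision is an SE of 0.5 × sqrt(1 − rho) against 0.25 SD, about 1.4 times wider at an assumed rho of 0.5. If that is judged too wide, the descriptive label alone is a cheaper remedy, but the window question then stays unanswered.

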### Intervention description {11a}

Both groups will receive the ICU-VR intervention during the study period, 3 (early) and 6 (late) months after hospital discharge. ICU-VR (duration: ±14 min) comprises several modules explaining the aspects of ICU treatment that are known to be the most frightening [24, 35]. The content was previously determined by a multidisciplinary team and has been demonstrated to be safe [32, 33]. For COVID-19 ICU survivors, we adapted the latter module by adding additional COVID-19 specific aspects of ICU treatment (i.e. mechanical ventilation in prone position, tracheostomy and isolation measures). In addition, information regarding SARS-CoV-2 and COVID-19 was added, and the voice-over was changed accordingly. Real ICU nurses and physicians were used to re-enact a typical day/treatment for a mock patient undergoing ICU treatment for COVID-19.

ICU-VR is hospital-specific, to expose patients to the actual environment where they were treated. As such, each hospital has its unique ICU-VR. An overview of the ICU-VR intervention of the Erasmus MC is depicted in Fig. 1, and the film script can be found in Additional file 1 (translated from Dutch to English). The intervention will be watched via head-mounted display (HMD-)VR glasses (Oculus Go, Irvine, CA, www.oculus.com/go), and patients will be allowed to move their head freely as to experience all aspects of the virtual environment.

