Patients’ satisfaction with and rating of ICU care and aftercare was based on the Patient Satisfaction Questionnaire and Family Satisfaction with ICU Care tools, altered to the needs of this study [43–45]. Additional novel items were added to evaluate patients’ perspectives on the ICU-VR intervention.

This questionnaire comprised 21 items, categorized in four sections: (1) satisfaction with and rating of ICU care and ICU aftercare and the added value of ICU-VR; (2) overall perspectives on the ICU-VR intervention; (3) perspectives on the content of ICU-VR; and (4) perspective on the effect of ICU-VR. Questions regarding ICU-VR were only answered by patients who had received the intervention, questions regarding satisfaction and rating by all patients. Psychological well-being and health-related quality of life will be assessed at 3, 4, 6, 7 and 12 months after hospital discharge. Satisfaction with and rating of ICU care and aftercare and perspectives on ICU-VR were administered by telephone during the study period after the first outpatient clinic visit. Baseline demographics and treatment-related characteristics, including, but not limited to, age, gender, race, pre-existing comorbidities, hospital and ICU length of stays, mechanical ventilation-related data (duration, prone positioning, highest PaO_2_/FiO_2_ ratio, occurrence of delirium, sedation, illness severity scores (APACHE IV, SAPS II)), mortality and medication, will be retrieved from electronic patient records.

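### Two of the three window-of-opportunity contrasts need 9-month scores that the plan never collects

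*Protocol article*

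**What the plan says.** Exposure times are fixed in Intervention description {11a}: "Both groups will receive the ICU-VR intervention during the study period, 3 (early) and 6 (late) months after hospital discharge".

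Statistical methods {20a} then plans an analysis of time-specific windows of opportunity, in which the groups are compared at equal time since ICU-VR. It names the months for each of three lags:

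- The first lag, 1 month, sets month 4 in the early group against month 7 in the late group.
- The second lag is worded "3 months (6 and 9 months after hospital discharge in the early and late intervention groups, respectively".
- The third lag is worded "6 months after receiving ICU-VR (nine and 12 months after hospital discharge in the early and late intervention groups, respectively".

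The models are mixed linear or logistic regressions with a random site intercept and a time-by-randomization interaction. The form in which time enters is not given.

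The collection schedule appears three times:

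- Plans for assessment and collection of outcomes {18a}: "Psychological well-being and health-related quality of life will be assessed at 3, 4, 6, 7 and 12 months after hospital discharge".
- The Fig. 2 legend: "Psychological well-being and quality of life will be assessed 3, 4, 6, 7 and 12 months after hospital discharge using follow-up questionnaires".
- Participant timeline {13}: "Questionnaires will be sent at 3 months (prior to the first outpatient clinic visit), 4 months, 6 months", with the same sentence ending "7 months and 12 months after hospital discharge".

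None of these lists month 9, and none gives a different schedule for either group.

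**The concern.** The analysis section relies on a visit that the data collection sections do not contain. The 3-month contrast needs late-group scores at month 9, and the 6-month contrast needs early-group scores at month 9.

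The timing question is a real aim of the trial. The Discussion says the best timing of ICU-VR is not known, and gives uncertainty about a later intervention as the reason for studying exposure at 6 months in the control group. The window analysis is the only one in the article framed to answer that question. If the text stays as it is, the analyst must decide after data collection what to put in the empty cells: imputed values for every patient in one arm, scores from month 7 or month 12, a modelled curve, or nothing. The first three would produce a result set by the chosen device and not by 9-month data. The fourth would leave the analysis silently incomplete.

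**Working it through.** **Inputs.** ICU-VR at month 3 (early) and month 6 (late), from {11a}. Lags of 1, 3 and 6 months, from {20a}. Collected months {3, 4, 6, 7, 12}, from {13}, {18a} and the Fig. 2 legend.

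**Step 1: reproduce the plan's own months.** Month needed = month of ICU-VR + lag.

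- Early: 3 + 1 = 4; 3 + 3 = 6; 3 + 6 = 9.
- Late: 6 + 1 = 7; 6 + 3 = 9; 6 + 6 = 12.

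All six agree with the months printed in {20a}. Month 9 is therefore no typing slip: it follows from the exposure times, and the article gives it twice, once as a numeral and once as a word.

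**Step 2: check each month against the schedule.**

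| Lag after ICU-VR | Early group | Late group | Observed in both arms? |
|---|---|---|---|
| 1 month | month 4, collected | month 7, collected | yes |
| 3 months | month 6, collected | month 9, not collected | no |
| 6 months | month 9, not collected | month 12, collected | no |

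Four of six cells are observed, and one of three contrasts has data in both arms. Each failing contrast lacks one arm, not both.

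**Step 3: look for another usable lag.** Lag = collected month − month of ICU-VR.

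- Early: 4 − 3 = 1; 6 − 3 = 3; 7 − 3 = 4; 12 − 3 = 9.
- Late: 7 − 6 = 1; 12 − 6 = 6.

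The only lag common to both groups is 1 month. Month 12 is 9 months after exposure in the early group and 6 months after in the late group, so it gives no lag-matched contrast.

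**Step 4: test the plan's missing-data methods ({20c}).** Multiple imputation needs some patients with the variable observed, and month 9 is observed in none. Last observation carried forward would use the month-7 score. In the late group that is the score 7 − 6 = 1 month after ICU-VR, relabelled as 3 months. In the early group it is the score 7 − 3 = 4 months after, relabelled as 6 months.

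**Step 5: could month 9 still be collected?** Eligible discharges began on March 29, 2020 ({10}), so the earliest 9-month date is about December 29, 2020. Trial status reports that recruitment started on June 29, 2020, three months after that first discharge date, and ended on February 3, 2021. For the earliest patients month 9 had therefore already passed when the article was written.

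**The case against.** The contradiction itself is not in dispute. The case on the other side concerns its weight, its wording and the remedy.

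- **Weight.** The primary outcome runs to 6 months after discharge and all its data are collected. The window analysis is not named under Objectives {7} or Outcomes {12}, and the named secondary comparison up to 12 months can be run. This is correct and limits the reach of the problem. It does not change the fact that a stated analysis cannot be carried out on the stated data.
- **Not strictly impossible.** {20a} does not say whether time is categorical or continuous. With continuous time, a model could interpolate month 9 between months 7 and 12. That is true, but the estimate would then rest on a trajectory that the article never specifies. The accurate statement is that the contrasts cannot be computed from observed scores.
- **Which side is wrong?** The article condenses a fuller protocol, so a 9-month questionnaire might have been left out of the text. Three matching statements of the schedule make an error in the analysis sentence more likely, but the full protocol should be checked. If no 9-month questionnaire exists there, the contrasts have to go.
- **Redundancy.** An early-against-late comparison at month 12 is already covered by the follow-up analysis. This stands. Its place in the fix is only to make clear what month 12 can and cannot be used for.

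**Conclusion.** The concern holds. On the schedule as published, two of the three window-of-opportunity contrasts have no observed outcome in one arm: late at month 9 for the 3-month lag, and early at month 9 for the 6-month lag. Those two of six cells are 100% missing by design. The question of when to offer ICU-VR can be answered at matched time since exposure only at 1 month (month 4 against month 7).

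This rests on one assumption: that the schedule stated in {13}, {18a} and the Fig. 2 legend is the one in use. The primary outcome, the sample size of 80 and the early-against-late comparisons at the collected months are not affected. The sections must be reconciled before analysis, because as written the analysis section promises results that the data cannot give.

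**What to change.** Check {13}, {18a}, the Fig. 2 legend and {20a} against the full protocol and make them agree. If no 9-month questionnaire exists:

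1. Delete the 3-month and 6-month post-exposure contrasts from {20a}.
2. Restrict the timing analysis to months 3, 4, 6 and 7, with the lag-matched comparison at 1 month only.
3. Use month 12 solely as an early-against-late comparison at equal time since discharge.
4. State that 9-month values will not be imputed, carried forward or replaced by scores from month 7 or month 12.

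Adding a 9-month questionnaire in both groups would restore all six cells and all three contrasts, but it is an option only if every patient can still receive it. On the article's dates that is unlikely for the earliest patients.

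The cost is a change of wording in the analysis section and the loss of two contrasts that could not have been produced. The sample size and the primary analysis stay as they are.

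### The timing model puts repeated scores per patient into one regression but names only a site intercept, so its time-by-group standard error is too large and some pooled group differences look too precise

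*Protocol article*

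**What the plan says.** Statistical methods {20a} describes three kinds of model.

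- Group differences at a given follow-up time: a mixed model with a site intercept. Each patient has one score, so no patient effect is needed.
- Differences throughout follow-up: a mixed model with a time-by-group interaction and "a random intercept and/or slope for each individual and each study site as appropriate".
- The timing analysis, which asks whether the effect depends on receiving ICU-VR at 3 or at 6 months: models at 1, 3 and 6 months after the intervention, "using mixed effect linear/logistic regression models with a random intercept for each site and an interaction variable time*randomization".

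In months since discharge, the timing model's three points are "4 and 7 months after hospital discharge in the early and late intervention groups, respectively", "6 and 9 months after hospital discharge in the early and late intervention groups, respectively" and "nine and 12 months after hospital discharge in the early and late intervention groups, respectively". The schedule in Plans for assessment and collection of outcomes {18a} reads: "Psychological well-being and health-related quality of life will be assessed at 3, 4, 6, 7 and 12 months after hospital discharge". It has no 9-month questionnaire.

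No residual correlation structure or robust variance is mentioned for the timing model.

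**The concern.** An interaction of time with group is defined only when at least two times sit in the same model, so each patient contributes more than one row. With a site intercept as the only random effect, two scores from one patient are treated as no more alike than scores from two patients of the same hospital. A hospital effect absorbs differences between the four hospitals. It does not absorb the correlation between one patient's repeated IES-R, HADS, EQ-5D or RAND-36 scores.

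This is not detail left to an analysis plan. The article states the random effects of this model, and it names the individual effect one sentence earlier for another model.

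Ignoring the correlation does opposite things to different contrasts. Contrasts within patients (change over time, and the time-by-group interaction) get standard errors that are too large. Contrasts that combine a patient's scores into a pooled or interpolated level get standard errors that are too small. At stake is the reading of the timing question, which the Discussion treats as open: a real difference in trajectory could be missed, and a pooled early-versus-late difference could look firmer than it is.

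**Working it through.** **Inputs.** The plan gives no figure for the timing model itself. Its alpha comes from Sample size {14}: "using a two-sided alpha of 0.05", with "a power of 0.80". The sample size there, 80, reproduces. An effect size of 0.77 with a rank test at its minimum relative efficiency of 0.864 (the article says no distribution was assumed) needs 32 per arm; 2 × 32 = 64, and 64/0.8 = 80. The number per arm cancels from every ratio below. The within-patient correlation r is not stated. I assume 0.5 to 0.7 and show 0.3 to 0.8, with equal variances and the same correlation between any two times.

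**Method.** Let k be the model standard error divided by the true one. The actual type I error is 2Φ(−1.96k).

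**Times that exist.** Of the three named points, the early group has 1 and 3 months after ICU-VR (4 and 6 months after discharge). The late group has 1 and 6 months (7 and 12 after discharge). With categorical time that is four observed group-by-time cells for six fixed-effect parameters, so the full interaction cannot be estimated. With linear time the model can be fitted.

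**Interaction.** The true variance of a patient's change between two times is 2(1 − r)σ²; the model takes it as 2σ². So k = 1/√(1 − r). This holds for the collected times with linear time, and for three complete categorical times.

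- r = 0.5: k = 1.41, type I error 2Φ(−2.77) = 0.6%.
- r = 0.7: k = 1.83, type I error 2Φ(−3.58) = 0.03%.
- Power, for an effect with true 80% power (1.96 + 0.84 = 2.80 true standard errors): Φ(2.80 − 2.77) = 51% and Φ(2.80 − 3.58) = 22%.

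**Group difference at t months after ICU-VR, collected times, linear time.** Each arm's line passes through its two means. The weight on the later mean is w = (t − 1)/2 in the early arm and v = (t − 1)/5 in the late arm.

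- Model variance is proportional to A = w² + (1 − w)² + v² + (1 − v)².
- True variance is proportional to A + rB, with B = 2w(1 − w) + 2v(1 − v).
- k = √(A/(A + rB)).

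Results:

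- t = 1: B = 0, so k = 1 and the type I error is 5%.
- t = 2: A = 1.18, B = 0.82. At r = 0.5, k = √(1.18/1.59) = 0.86, giving 9%. At r = 0.7, k = √(1.18/1.754) = 0.82, giving 11%.
- t = 3: A = 1.52, B = 0.48. At r = 0.5, k = √(1.52/1.76) = 0.93, giving 7%. At r = 0.7, k = √(1.52/1.856) = 0.90, giving 8%.

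**Average of three scores per patient (hypothetical).** k = 1/√(1 + 2r), giving 17% at r = 0.5 and 21% at r = 0.7.

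**Type I error over a wider range of r (nominal 5%).**

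| Contrast | r = 0.3 | 0.5 | 0.7 | 0.8 |
|---|---|---|---|---|
| Time-by-group interaction | 1.9% | 0.6% | 0.03% | <0.1% |
| Group difference at 2 months, collected times, linear | 7.5% | 9.1% | 10.8% | 11.6% |
| Group difference at 3 months, collected times, linear | 6.1% | 6.9% | 7.6% | 8.0% |
| Group difference at one time, categorical | 5% | 5% | 5% | 5% |
| Average of three scores (hypothetical) | 12% | 17% | 21% | 22% |

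**Check by simulation.** 20,000 trials per correlation, three complete times, site entered as a fixed effect to stand in for the site intercept. At r = 0.5 and 0.7 the averaged group difference erred in 16.8% and 21.0% of trials, and the interaction in 0.7% and 0.05%. Analysing at patient level, which in balanced data is equivalent to a patient intercept, gave 5.2% and 5.1%, and 5.0% and 4.9%.

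**The case against.** The best defence is that the article names no time-averaged contrast. It says outcomes will be analysed at 1, 3 and 6 months after ICU-VR, which can be read as a group difference at each time. With categorical time and equal variances, that difference has a correct standard error even without a patient effect. The interaction error is conservative and creates no false positives. This stands as far as it goes. It does not rescue the interaction, which the plan names explicitly and which loses power. Nor does it cover an interpolated difference under linear time. Reading the sentence as separate models per time point fails too, because the interaction would then be undefined.

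A reader might infer three stronger things that the documents do not support.

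- That false positives reach 17% to 21%. This needs three scores per patient, averaged over time. No 9-month questionnaire is scheduled, and the average is not a stated contrast.
- That every test of the timing question is invalid. The single-time comparison is not affected, and 1 month after ICU-VR is a point that both arms share.
- That four hospitals make the random site intercept wrong and site should be fixed everywhere. A random intercept is an accepted way to handle the stratification factor, and no material harm follows. If the site variance were estimated as zero and site dropped out, type I error would be 2Φ(−1.96/√(1 − ICC)): about 4.8% at an intraclass correlation of 0.02 and 4.4% at 0.05.

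**Conclusion.** The point holds, limited to the timing model, as a should-fix. Followed as written, the model omits a patient effect that its repeated scores require. The direction of the interaction error holds for any positive within-patient correlation; its size depends on a correlation that the article does not give. The upward error for the group difference is modest on the collected times and depends on treating time as linear.

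The per-time-point models have one score per patient, and the throughout-follow-up model names an individual effect. The primary outcome is the effect up to 6 months, and the Outcomes section does not list the timing comparison as an outcome. So the primary comparison and the sample size of 80 do not change.

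The figures are for the linear models. For the logistic models no size was computed; there, leaving out the patient effect also changes the odds ratio from a patient-specific to a population-averaged one.

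**What to change.** In the timing paragraph of Statistical methods {20a}, add a random intercept for each patient alongside the site intercept, or state an equivalent within-patient covariance. This matches the model in the preceding sentence. It costs one phrase, with no extra data and no change to the sample size. The site intercept can stay.

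The 9-month points need their own correction. The timing model calls for them in both arms and the questionnaire schedule does not supply them. A patient effect does not make the full categorical interaction estimable, so the two sections must be reconciled separately.
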